#### Representative groups

2.7.3

The LCR groups will be generated from each LCE group by applying the selected control factors to lung cancer patient samples. The selected samples from LCEX group will be included in the lung cancer representative Xu (LCRX) group. Likewise, the selected samples from LCES group will be assigned to the lung cancer representative Stasis (LCRS) group while samples from LCEG group will be included in the lung cancer representative Gentleness (LCRG) group. The representative samples must be selected to have the same numbers of samples in each control factor for all pattern identification groups. It is also crucial to select a sufficient number of samples in order to reflect each pattern identification group. The number of patients with each control factor will be kept constant in each representative group.

#### Scientific validation of entire groups using representative groups

2.7.4

Comparison of the identified glycoproteins between the LCE groups and the LCR groups with the same pattern identification type may reveal whether each LCR group truly represents each LCE group. This will be used to validate the unique glycoproteins from each pattern identification type of lung cancer patients under the framework of TKM.

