#### Sample groups on LCE groups

2.6.3

All the lung cancer patients will be divided into 3 LCE groups according to their pattern identification types (Xu, Stasis, or Gentleness). The patients who will be assessed as Xu will belong to lung cancer entire Xu (LCEX) group. Likewise, the patients who will be assessed as Stasis will be included to lung cancer entire Stasis (LCES) group, while patients to be assessed as Gentleness will belong to lung cancer entire Gentleness (LCEG) group.

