#### Definition of representative sample

2.7.1

Sampling is particularly crucial when heterogeneous materials are analyzed. It is critical that the analysis aims are clearly declared and that an appropriate sampling procedure is adopted. In some situations, a sampling strategy needs to be devised in order to optimize the value of the analytical information collected. A representative sample is what truly reflects the composition of the material to be analyzed within the context of a defined analytical problem.^[42]^

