#### LCR groups (LCRX, LCRS, and LCRG)

2.8.2

All LCR groups must have the same number of samples. The number of samples in these 3 LCR groups will be set by setting all the control factors other than pattern identification constant.

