(1)the glycoprotein comparison sets from the first and second MS/MS runs for the confirmation of reproducibility(2)the glycoprotein comparison sets from the 2 protein search engines to increase the confidence level of identified proteins(3)the glycoprotein comparison sets between LCE groups and LCR groups to check the representativeness(4)the unique and intersection glycoproteins set by comparison of LCE groups (LCEX, LCES, and LCEG) based on their pattern identifications assessed from BCQs of the lung cancer patients(5)the unique and intersection glycoproteins set by comparison of LCR groups (LCRX, LCRS, and LCRG) based on their pattern identifications assessed from BCQs of the lung cancer patients.

The overall data processing and analysis procedures are described in Figure 2. Unique glycoproteins from each group with each pattern identification of lung cancer patients will be generated from the results.

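### Each LCR pool is drawn from its own LCE pool, so LCE-LCR agreement is inflated by shared patients and cannot validate the unique glycoproteins

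*Protocol article*

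**What the plan says.** All references are to the protocol article.

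- **Who is in LCE.** Section 2.6.3: "All the lung cancer patients will be divided into 3 LCE groups according to their pattern identification types (Xu, Stasis, or Gentleness". Nothing removes anyone from these groups later.
- **Who is in LCR.** Section 2.7.3: "The LCR groups will be generated from each LCE group by applying the selected control factors to lung cancer patient samples". Section 2.9 then pools plasma for every LCE and every LCR group, six pools in all.
- **How LCR is composed.** Section 2.7.3: "The representative samples must be selected to have the same numbers of samples in each control factor for all pattern identification groups". Section 2.8.2: "All LCR groups must have the same number of samples". Section 2.7.2 lists factors that may be chosen and definitely restricts LCR to patients with no earlier cancer other than lung cancer.
- **What representative means.** Section 2.7.1: "A representative sample is what truly reflects the composition of the material to be analyzed", a definition tied to the analytical problem in hand.
- **What the comparison is for.** Section 2.7.4 gives two uses. It "may reveal whether each LCR group truly represents each LCE group", and then: "This will be used to validate the unique glycoproteins from each pattern identification type of lung cancer patients under the framework of TKM". Comparison (3) in section 2.13 repeats the first use: "the glycoprotein comparison sets between LCE groups and LCR groups to check the representativeness".
- **Sizes.** Section 2.8 plans 100 participants with at least 10 in each LCE group. It gives no number for LCR.

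**The concern.** A validation set is meant to show that a finding recurs in patients who did not generate it. Here the same people supply both lists. A glycoprotein that appears only in the Stasis LCE pool because of a few unusual patients will tend to appear only in the Stasis LCR pool if those patients are selected.

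The other checks in section 2.13 do not fill the gap. Comparisons (1) and (2) address run-to-run reproducibility and search-engine agreement, not recurrence in other patients. No held-out or independent patients are described. Yet section 3 expects the proteins to be categorised as indicators (biomarkers) of each pattern, so chance differences between pools could be carried forward as validated ones.

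A second difficulty is that LCR is asked to do two things. It must reflect its parent group, and it must have the same control-factor mix as the other two LCR groups. These pull apart when the parents differ.

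**Working it through.** The plan gives no figure for this comparison, so there is none to reproduce. Three checks follow.

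**1. Overlap of the pools**

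Inputs: n patients in an LCE group and m of them in its LCR group. The minimum n of 10 and the total of 100 come from section 2.8. Every m is assumed, and n = 33 assumes a roughly equal three-way split of 100.

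For independent patients with common variance s² and no pattern effect:

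- variance of the LCR mean = s²/m
- variance of the LCE mean = s²/n
- covariance of the two = s²/n
- correlation = (s²/n) / sqrt((s²/m)(s²/n)) = sqrt(m/n)

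| LCR m | LCE n | sqrt(m/n) |
|---|---|---|
| 10 | 80 | 0.35 |
| 10 | 33 | 0.55 |
| 5 | 10 | 0.71 |
| 8 | 10 | 0.89 |
| disjoint patients | any | 0 |

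Section 2.8.2 makes m the same for all three patterns, so m/n is largest where n is smallest. With LCE groups of 80, 10 and 10 and m = 8, the correlation is sqrt(8/80) = 0.32 in the large group and sqrt(8/10) = 0.89 in each small one. The apparent confirmation is most inflated where the evidence is thinnest.

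**2. Effect on lists of detected proteins**

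The protocol compares lists, not means, so the direction was checked by simulation with no pattern effect. The assumptions, none of them from the protocol, were:

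- 400 proteins and 300 repetitions
- log-scale SD of 0.7 between proteins, 1.0 between patients and 0.1 for technical error
- detection when the pool mean exceeds a fixed threshold
- unique means detected in exactly one of the three pattern pools
- the LCR subset is taken without regard to covariates

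The table gives the share of chance LCE-unique proteins that are again unique to the same pattern in the second set of pools.

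| LCE sizes | m | Nested LCR | m new patients |
|---|---|---|---|
| 10/10/10 | 5 | 44.3% | 12.0% |
| 10/10/10 | 8 | 59.1% | 11.6% |
| 10/10/10 | 10 | 69.9% | 10.5% |
| 33/33/34 | 10 | 32.1% | 13.4% |
| 33/33/34 | 30 | 51.0% | 11.0% |
| 45/45/10 | 5 | 30.2% | 13.0% |
| 80/10/10 | 8 | 47.0% | 12.1% |

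Every protein counted here is a false lead. Nesting confirms about 30% to 70% of them, against about 11% to 13% in new patients.

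**3. Matching against representativeness**

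Suppose a control factor has shares p1, p2 and p3 in the three LCE groups and one common share c in the three LCR groups. The smallest achievable value of the largest gap is (max p − min p)/2. The shares below are illustrative.

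- 70/50/30%: (70 − 30)/2 = 20 points
- 60/50/40%: (60 − 40)/2 = 10 points
- 50/50/50%: 0 points

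The prior-cancer restriction works the same way. Any LCE group that contains patients with another earlier cancer has an LCR group that contains none.

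**The case against.** The best defence is that LCR serves mainly to control confounding. Sections 2.7.2 and 3 say that sex, age, smoking, stage and similar factors may affect glycosylation. Re-analysis in a matched subset is a recognised sensitivity analysis, and nesting does not defeat it. A unique glycoprotein that vanishes after matching is a useful warning. This stands, and the fix keeps that use. Disagreement is still ambiguous, since it may also reflect a smaller pool or missed detection, but it is not uninformative.

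A reader might infer that agreement is guaranteed and the comparison worthless. The documents do not support that. Each pool is captured, digested and run separately (sections 2.9 to 2.12), so recurrence partly tests technical repeatability. In the simulation nested LCR also failed to confirm about 30% to 70% of chance findings.

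A reader might also infer that at most one LCR group can mirror its parent. That is false: with shares of 50/50/30%, LCR groups set at 50% match two parents exactly. It follows only that not all three can match, and only if the parents differ. Most control factors are offered as options in section 2.7.2; only the prior-cancer restriction is definite.

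It is fair, too, that the definition in section 2.7.1 is relative to the analytical problem, that representativeness is to be checked rather than assumed, that sqrt(m/n) describes continuous means, and that section 2.8 calls the trial preliminary. None of this supplies the independent patients that validating the unique glycoproteins would need.

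**Conclusion.** The validation claim in section 2.7.4 is not supported by the design. Sections 2.6.3, 2.7.3 and 2.9 put LCR patients' plasma in both pools of the same pattern, so agreement is inflated, most of all in the smallest pattern group.

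The size depends on LCR numbers that the article does not give. The correlation of sampling errors is 0.55 for 10 of 33 and 0.89 for 8 of 10. It assumes independent patients with equal variance and no pattern effect. The simulated percentages rest on assumed variances and an assumed detection threshold, and should be read for direction only.

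The representativeness point is conditional: the three LCR groups cannot all reflect their parents if the LCE groups differ on the matched or restricted factors. The documents do not say whether they will, although concern about such factors is the reason given for matching.

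The LCR-versus-LCR comparison (5) is not undermined by the overlap and remains a reasonable matched comparison of patterns.

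**What to change.** In section 2.7.4 and comparison (3) of section 2.13:

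- Describe LCR as a covariate-matched subset of LCE, and LCE versus LCR as a sensitivity analysis for confounding by the control factors.
- Remove the statements that this comparison validates the unique glycoproteins or shows representativeness, and align the corresponding wording in section 3.
- Treat LCR versus LCR (comparison 5) as the confounder-controlled comparison of patterns.
- Report unique glycoproteins as exploratory until they have been tested in patients outside the discovery pools.

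The cost is a weaker conclusion than the one now stated. Samples, pools and runs are unchanged.

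Splitting each pattern into LCR and LCE-minus-LCR pools would remove the overlap, but it is optional. The remainder would differ from LCR on the control factors and would hold all patients with other prior cancers. It could also be very small (10 − 8 = 2 patients in the smallest permitted group if 8 are matched), and the split would give up the whole-group pools that sections 2.6.2 and 3 consider important.

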### Sample size

2.8

As a preliminary trial for exploring proteomics approach based on pattern identification, we intend to enroll 100 participants.

#### LCE groups (LCEX, LCES, and LCEG)

2.8.1

At least 10 patients will be assigned to each group.

#### LCR groups (LCRX, LCRS, and LCRG)

2.8.2

All LCR groups must have the same number of samples. The number of samples in these 3 LCR groups will be set by setting all the control factors other than pattern identification constant.

### Samples preparation

2.9

Ten milliliters of blood will be withdrawn from each lung cancer patient before surgery and mixed on a blood mixer at room temperature. The mixed blood will be centrifuged for plasma separation from blood cells and the supernatant plasma will be transferred to a tube and stored in −80°C deep freezer until filtration. All the plasma samples will be filtered and pooled together according to each LCE group and LCR group. The 6 pooled samples will be stored in a −80°C deep freezer until affinity selection.

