#### Primary outcomes

2.2.1

1.Diagnosis of each pattern identification of Korean lung cancer patients with BCQs.2.Verification of the correlation of BCQ and blood on each patients’ pattern identification type through glycoproteomics.3.Protein identification and categorization by patients’ pattern identification for patient-specific diagnosis and medication in TKM.

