### Glycoprotein capture

2.10

Glycoprotein capturing lectin column will be self-packed and connected to high performance liquid chromatography (HPLC) system for lectin affinity chromatography (LAC). Pooled human plasma from lung cancer patients will be loaded directly onto the column with mobile phase. The detailed affinity chromatographic method will follow the method section of the reference paper.^[43]^

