### nLC-MS/MS methods for protein identification

2.12

The PNGase F-treated peptide mixtures from the 6 groups (LCEX, LCES, LCEG, LCRX, LCRS, and LCRG) will be analyzed with a nano liquid chromatography-tandem mass spectrometry (nLC-MS/MS). Each sample will be run more than twice under the identical conditions. The operational instruments and detailed methods will be in the method section of the reference paper.^[45]^

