### Statistical analysis with database searches

2.13

After at least 2 MS/MS data are obtained from each sample, protein identification will be performed with 2 complementary database search programs. Both Proteome Discoverer 1.4 (Thermo Fisher Scientific Inc., USA) and ProteinPilot 5.0 (SCIEX, USA) will be used to identify proteins from MS and MS/MS spectra. Each software program has its own unique analysis algorithm. Thus, it will be meaningful to compare the results from the 2 programs because it will reinforce the confidence of the identified proteins. At least 4 data files with identified proteins will be produced from each sample. Each data file will be individually sorted and filtered under the following conditions:

(1)dynamic modification option: deamidated (N-glycosylation)(2)peptide confidence levels: the peptide is significant only if (a) confidence levels are over 95%, or (b) confidence levels are below 95% in 2 runs but show significant MS/MS spectra.(3)proteins inclusion and exclusion: for Proteome Discoverer software, only the proteins with protein scores of 6.0 or higher will be included; for ProteinPilot software, only the proteins with the unused values of 2.0 or higher will be included. The rest of the identified proteins will be excluded from the results.

Starting with the significant data from the 2 software programs, only the peptides/proteins with N-glycosylation sites will be selected and used for the parent protein identification. These glycoproteins will be sorted and compared within each group (Xu, Stasis, and Gentleness). Then these proteins will be sorted into those that are identified in all LCE groups, all LCR groups, and only certain group(s). The resulting 6 N-glycoprotein lists will be used for the following 5 comparative analyses:

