## Discussion

3

This is the first study in Korea to diagnose pattern identification with BCQ assessment which was proven to obtain validity and reliability in Taiwan^[39–40]^ and Hong Kong^[41]^. This study is also the first to apply BCQ assessment to lung cancer patients. Furthermore, this is the first to correlate BCQ and patients’ blood through glycoproteomics. After diagnosis of pattern identification type with BCQ, glycoproteomics approach will be introduced to all the plasma in order to establish scientific and biomedical criteria on BCQ for the first time. Two sets of patients’ plasma will be explored from each pattern identification type of TKM; a holistic evaluation (LCE groups) and a scientific validation of the representativeness (LCR groups). It is regarded that the diseases of a patient with specific pattern identification arise from the corresponding pattern identification. Thus, it is important to holistically analyze the entire lung cancer patients according to their pattern identification types. On the other hand, by carefully selecting appropriate control factors, all the control factors other than the pattern identification are prevented from interfering with the change in glycoproteins in their blood. This change may vary depending on diverse variables such as sex, age, and medical history.

The patient-optimized TKM for lung cancer can be applied to cancer therapy for future clinical trials and treatments by presenting scientifically valid criteria on patient's pattern identification from this trial. The identified plasma proteins from each pattern identification type will be categorized as pattern identification indicators (biomarkers) for precision medicine. In the long run, these proteins can also be utilized as lung cancer biomarkers aiming for development of in vitro lung cancer diagnostic kits based on pattern identification of lung cancer patients.

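### One pool per pattern in each comparison, with repeat runs of that pool only, leaves no estimate of between-patient variation, so the verification and biomarker wording is not supported

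*Protocol article*

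**What the plan says.** All references are to the protocol article.

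- **Pooling (2.9).** "All the plasma samples will be filtered and pooled together according to each LCE group and LCR group". The result is six vials: "The 6 pooled samples will be stored in a" deep freezer until affinity selection.
- **Capture (2.10).** "Pooled human plasma from lung cancer patients will be loaded directly onto the column with mobile phase". No individual plasma sample is named as input.
- **Runs (2.12).** The "peptide mixtures from the 6 groups (LCEX, LCES, LCEG, LCRX, LCRS, and LCRG) will be analyzed", and "Each sample will be run more than twice under the identical conditions". Section 2.13 gives a different minimum: "After at least 2 MS/MS data are obtained from each sample, protein identification will be performed with 2 complementary database search programs".
- **Comparisons (2.13).** Five are listed: (1) first against second run, for reproducibility; (2) one search engine against the other; (3) LCE against LCR, for representativeness; (4) and (5) unique and shared glycoproteins across the three patterns, within LCE and within LCR.
- **Nesting (2.7.3, 2.7.4).** Each LCR group is selected from its LCE group. Agreement between the two is to be used to validate the unique glycoproteins of each pattern.
- **Claims.** Primary outcome 2 (2.2.1) begins "Verification of the correlation of BCQ and blood on each" and continues with the patient's pattern type, assessed by glycoproteomics. The Discussion adds: "The identified plasma proteins from each pattern identification type will be categorized as pattern identification indicators (biomarkers) for precision medicine".

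**The concern.** To say that a protein goes with a pattern, one must know how much it varies among patients who share that pattern. Once their plasma is merged, that information is gone and no later analysis can recover it. Repeat runs show how well the instrument reproduces one vial. Two search engines show how far software agrees on the same spectra. Neither bears on whether another set of patients with the same pattern would give the same list.

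At stake is what the trial may conclude. Outcome 2 is a primary outcome and is framed as verification. The Discussion then carries the proteins forward as pattern indicators for precision medicine and, in the long run, diagnostic kits. Both need evidence that differences between patterns exceed differences between patients.

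**Working it through.** **Inputs.** Six pools, three LCE and three LCR (2.9). Runs per pool: at least 2 (2.13) or more than 2 (2.12). LCR drawn from LCE (2.7.3). Enrolment 100, at least 10 per LCE group (2.8). The article derives the 100 from no stated error rate, power or effect size, so there is no figure to reproduce; 3 x 10 = 30 is compatible with 100.

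**1. Independent units.** Error df = pools - patterns.
- LCE: 3 - 3 = 0. LCR: 3 - 3 = 0.
- Taking LCE and LCR together does not help, because the LCR patients' plasma is in both.
- For contrast, individual assays would give 30 - 3 = 27 or 100 - 3 = 97.

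**2. What repeat runs measure.** For a pool of n patients in equal volume, run m times, the variance of its mean is (between-patient variance)/n + (technical variance)/m. Repeat runs estimate only the second term. A larger pool shrinks the first term, but the design cannot show by how much.

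The plan does not propose treating runs as replicates. If someone did, a one-way analysis of variance at nominal 5%, simulated with no true pattern difference (100,000 draws, assumed ratio of patient SD to technical SD from 0.5 to 3), would reject as follows:

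| Patients per pool | 2 runs | 3 runs |
|---|---|---|
| 10 | 5.3% to 17.1% | 5.7% to 32.1% |
| 33 (assumed even split) | 5.1% to 8.6% | 5.2% to 13.8% |

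**3. Unique proteins without a pattern effect.** If each of three pools independently detects a protein with the same probability p, it is found in exactly one with probability 3p(1-p)^2:

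| p (assumed) | Found in exactly one pool |
|---|---|
| 0.1 | 3 x 0.1 x 0.81 = 24% |
| 0.3 | 3 x 0.3 x 0.49 = 44% |
| 0.5 | 3 x 0.5 x 0.25 = 38% |
| 0.9 | 3 x 0.9 x 0.01 = 3% |

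Re-running the pool can reduce the part of this due to technical noise. It cannot reduce the part due to which patients are in the pool.

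**4. A sub-pool layout.** Take 4 sub-pools per pattern, 2 from LCR patients and 2 from the rest: 3 x 4 = 12.
- Matched and unmatched sub-pools are not exchangeable, so labels are permuted within stratum. Each stratum has 6!/(2!)^3 = 90 arrangements; together 90 x 90 = 8,100.
- For a statistic unchanged when the three patterns are renamed, the smallest p is 6/8,100 = 0.0007.
- Residual df with a stratum term: 12 - 3 - 1 = 8.
- The LCR stratum alone has 6 - 3 = 3 df and a smallest p of 6/90 = 0.067, so it cannot reach 0.05 by itself.
- Runs: 12 x 2 = 24, against 6 x 2 = 12 (2.13) or 6 x 3 = 18 (2.12) now planned.

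**The case against.** **It is preliminary.** Section 2.8 calls the trial a preliminary exploration, and 2.2.2 places biomarker discovery in a large population among the long-term outcomes. Outcome 2 names no patient-level coefficient or test and can be read as a group-level comparison. This stands as far as it goes: description by pattern pool is a legitimate aim, and pooling is not itself the fault. It does not cover the word verification in a primary outcome, or the label the Discussion gives to the identified proteins.

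**The LCE/LCR comparison is a check.** In part it is. A protein contributed by one unusual patient outside LCR would not be expected to recur in the LCR pool, and that would be an adverse result. A protein contributed by a patient inside LCR is present in both pools, so some of the agreement is built in.

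**Stronger readings that the article does not support.**
- A reader might infer that three pools must give three different lists, or that no result could count against the questionnaire. Comparisons (4) and (5) also report shared proteins, and comparison (3) can fail.
- A reader might infer that capture and digestion are not replicated. Those methods are referred to cited papers, so silence here shows nothing.
- A reader might infer that unequal group sizes dilute patients unequally throughout. The LCR groups must be equal in size (2.8.2), and the plasma volume per patient in the LCE pools is not stated.

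**Conclusion.** The point holds for inference, not for description. In each comparison the pattern effect has 0 error degrees of freedom, and enrolling more patients does not change that. Protein lists by pool, and primary outcome 1, remain achievable. Verification of a correlation between questionnaire and blood, and the status of pattern indicators or biomarkers, are not.

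The degrees-of-freedom count follows from the article alone. The 3% to 44% range depends on assumed detection probabilities shared by all patterns and on independent pools. The rejection rates depend on assumed variance ratios and apply only if runs are treated as replicates. These figures illustrate size; the conclusion does not rest on them.

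It would go too far to say that the trial must be redesigned. Rewording is enough to bring the claims into line with the data.

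**What to change.** **Needed, wording only.**
- In 2.2.1, restate outcome 2 as an exploratory description of glycoproteins by pattern pool.
- In the Discussion, call proteins found in one pattern only untested candidates.
- In 2.13, state that comparison (1) measures technical reproducibility only.
- In 2.7.4, state that LCE/LCR overlap is not independent validation.
- Reconcile the number of runs between 2.12 and 2.13.

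**Preferable, if plasma is not yet pooled.** Recruitment began in September 2015 (2.3), and the article does not say whether pooling has started. Split each pattern into independent sub-pools with equal patient numbers and equal plasma volume per patient, for example 2 from LCR patients and 2 from the others. Capture, digest and run each separately. Keep at least two runs per sub-pool, so that comparison (1) and the two-run peptide rule in 2.13 still work. Test whether dissimilarity between patterns exceeds that between sub-pools of the same pattern, permuting labels within the LCR and non-LCR strata. Read the matched LCR stratum as the less confounded comparison, since the other stratum may differ in sex, stage or smoking.

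**Cost of the sub-pool option.** It needs 12 captures and digestions instead of 6, and 24 runs against 12 to 18 (36 if more than two runs are meant, 12 x 3). Each capture has less plasma. At the minimum of 10 patients per pattern, four equal sub-pools hold 2 patients each, so 3 x 8 = 24 of the 100 would be used. The option fails if the smallest pattern group has too few patients outside LCR.
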